### Inclusion criteria

Patients of any sex who seek dental treatment at the Dentistry Clinic of *Universidade Metropolitana de Santos*.Be between 04 and 10 years old;Good general health;Present at least two tooth surfaces that can be included in the study.

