### Sample calculation

Sample size can be calculated from the sample size equation for comparing paired nominal data by using McNemar’s test [15]:

$$n=\frac{{\left[z_{\alpha /2}\sqrt{p_{01}+p_{10}}+z_{\beta }\sqrt{p_{01}+p_{10}-{\left(p_{01}-p_{10}\right)}^{2}}\right]}^{2}}{{\left(p_{10}-p_{01}\right)}^{2}}$$

Similar formulae can be obtained for the one-sided non-inferiority test by substituting *z*_*α*/2_, *p*_10_ with *z*_*α*_ and *p*_10_ + *M*:

$$n=\frac{{\left[z_{\alpha }\sqrt{p_{01}+p_{10}+M}+z_{\beta }\sqrt{p_{01}+p_{10}+M-{\left(p_{01}-p_{10}-M\right)}^{2}}\right]}^{2}}{{\left(p_{10}+M-p_{01}\right)}^{2}}$$

where significance level *α* = 0.05, power 1 –β = 0.8, non-inferiority margin M = 5%, assumed detection rate *p*_01_ = 0.06%, *p*_10_ = 0.1%

The minimum sample size required is 12 surfaces. Assuming the drop off rate to be 20%, an additional 25 surfaces will be recruited. So, the total number of surfaces needed for the clinical trial is 149, requiring 80 patients.

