### Organization and statistical treatment of data

Non-parametric McNemar’s Chi-Square test will be used for paired nominal data. This test enables the comparison of the detection proportions between the two methods. Kappa coefficients will be calculated to assess the agreement between the two methods.

Differences in detecting the existence of primary interproximal caries lesions above the gingiva (sensitivity and specificity) between the iTero Element 5D system and BWX and the corresponding 90% confidence interval for the differences will be calculated. A minimum of 154 surfaces will ensure a power of 0.8, with an alpha = 0.05. Moderate agreement (Kappa≥0.5) is expected between iTero Element 5D system and radiography. Non-inferiority of the iTero Element 5D is expected as compared with radiography and evaluated by the McNemar’s Chi-Square test.

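### The surface counts of 12, 149 and 154 cannot all be right: the plan's own formula gives 124 evaluable surfaces, and a 20% loss then calls for 155, not 149

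*Protocol article*

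**What the plan says.** Two sections of the protocol article give numbers of surfaces.

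- **Sample calculation.** A paired (McNemar) formula is adapted to a one-sided non-inferiority test. The inputs are "significance level *α* = 0.05", "power 1 –β = 0.8", a margin M of 5%, and assumed rates p01 = 0.06% and p10 = 0.1%. The section then states: "The minimum sample size required is 12 surfaces. Assuming the drop off rate to be 20%, an additional 25 surfaces will be recruited". It ends: "So, the total number of surfaces needed for the clinical trial is 149, requiring 80 patients".
- **Organization and statistical treatment of data.** "A minimum of 154 surfaces will ensure a power of 0.8, with an alpha = 0.05". Nothing says how this figure was derived, or whether it counts surfaces recruited or surfaces left for analysis.

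Two further statements bear on supply. Materials and methods plans 80 children in two groups of 40. Under Inclusion criteria each child must "Present at least two tooth surfaces that can be included in the study".

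**The concern.** On its face the Sample calculation section does not add up: 12 plus 25 is 37, not 149, and 25 is not 20% of 12. The total said to be needed after allowing for drop-off (149) is also smaller than the minimum for the same power and alpha given in the next section (154).

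Surfaces are the unit in which the sample size is expressed, and the comparison of the scanner with radiography is a non-inferiority claim that rests on the stated 80% power. As written, a study that stopped at 149 surfaces would satisfy one section and fall below the minimum of the other. A reader checking the power cannot tell which number the trial is held to.

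**Working it through.** **Inputs**, all from Sample calculation: one-sided α = 0.05, so z_α = 1.645; power 0.8, so z_β = 0.8416; M = 0.05; p01 = 0.0006; p10 = 0.001. The one-sided reading follows from the text ("Similar formulae can be obtained for the one-sided non-inferiority test by substituting" z_α for z_α/2) and fits the 90% confidence interval in the statistical section.

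**1. Required evaluable surfaces.** Write S = p01 + p10 + M and D = p10 + M − p01.

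- S = 0.0006 + 0.001 + 0.05 = 0.0516
- D = 0.001 + 0.05 − 0.0006 = 0.0504
- n = [z_α√S + z_β√(S − D²)]² / D² = [1.645√0.0516 + 0.8416√(0.0516 − 0.0504²)]² / 0.0504² = 123.48, so **124**

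**2. Reproducing the plan's 149.** 124 × 0.2 = 24.8, rounded to 25, and 124 + 25 = 149. Equivalently, 124 × 1.2 = 148.8. So the total and the added 25 both follow from 124, and neither follows from 12. No variant tried returns 12:

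- two-sided α: 158
- continuity correction: 143
- margin left out of the variance: 4 to 5
- rates read as proportions 0.06 and 0.10: 159

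**3. Drop-off.** If 20% of recruited surfaces are lost, keeping 124 needs 124/(1 − 0.20) = **155**. Multiplying by 1.2 falls short: 149 × 0.8 = 119.2, about 119, which is 5 below 124.

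**4. Power**, from the same formula solved for power: Φ{[√n·D − z_α√S] / √(S − D²)}.

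| Evaluable surfaces | How reached | Power |
|---|---|---|
| 119 | 149 recruited, 20% lost | 0.787 |
| 124 | required by the formula | 0.801 |
| 128 | 160 recruited, 20% lost | 0.813 |
| 154 | if 154 means evaluable | 0.872 |

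**5. The 154.** 123.48/0.8 = 154.35, so 154 is close to the requirement of step 1 correctly inflated before rounding up, that is, a number to recruit. Other routes also reach it. Exchanging the two rates gives 127.56, so 128, and 128 × 1.2 = 153.6. A two-sided calculation with rates of 0.06 and 0.10 and the margin left out of the variance gives 153.49, which would be a number before drop-off. The arithmetic therefore leans towards a figure after drop-off but does not settle it. If 154 is meant as evaluable, recruitment would be 154/0.8 = 192.5, so 193.

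**6. Supply from 80 children.** 80 × 2 = 160 surfaces at least, and 160 × 0.8 = 128 at least after a 20% loss. The 160 exceeds 149, 154 and 155, and the 128 exceeds 124.

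**The case against.** The strongest reply is that nothing in the trial as planned depends on the error. Enrolment is by child, and 80 eligible children bring at least 160 surfaces, which after a 20% loss still give 0.813 power by the plan's formula. The 12 is almost certainly a lost digit and not a target anyone would recruit to. The 154 has a benign reading that nearly coincides with the correct 155. Even if recruitment stopped at 149 surfaces, the loss is about 1.5 percentage points of power (0.801 to 0.787).

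Most of that stands, and it rules out two stronger readings that a reader might infer.

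- *That the planned enrolment misses the required number.* The documents do not show this. It is true of the stated total of 149, but 80 children supply more than 155. A shortfall would arise only against a minimum of 154 evaluable surfaces, with children contributing about two each (128 left), and the article does not say that 154 is evaluable.
- *That 149 surfaces from 80 children, 1.86 per child, contradicts the two-surface criterion.* It does not. The 149 is a number needed, not a planned yield. At two surfaces each, 75 children would already supply it, so 80 meet the need with some surplus.

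What the reply does not remove is that the printed minimum is wrong, that the drop-off is applied by the wrong rule, and that two sections give different totals for the same power and alpha. Correcting the 12 alone would leave the other two errors in place.

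**Conclusion.** The point holds as a set of wrong and conflicting figures in the sample size justification. By the plan's own formula the requirement is 124 evaluable surfaces, where 12 is printed. The number to recruit at 20% loss is 155, where 149 is printed, a gap of 6 surfaces. Taken literally, 149 recruited gives about 119 evaluable and 78.7% power against the stated 80%. The 154 conflicts with the 149 and is undefined as to drop-off. Depending on the reading, it is about one surface below the correct total or implies 193 to recruit.

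The consequence for the trial itself is small, because 80 children with at least two surfaces each cover 155.

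This rests on three assumptions: the printed percentages are taken literally, surfaces are treated as independent, and the 20% loss applies to surfaces. Read as proportions of 0.06 and 0.10, the rates would give 159 evaluable and 159/0.8 = 198.75, so 199 to recruit, which 160 would not cover. That reading does not reproduce the plan's 149, so it is not evidently the one used.

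**What to change.** State one chain, identically, in Sample calculation and in Organization and statistical treatment of data:

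- 124 evaluable surfaces by the stated one-sided formula and inputs;
- 124/0.8 = 155 surfaces to recruit, allowing for 20% loss;
- covered by 80 children with at least two eligible surfaces each, giving at least 160 recruited and at least 128 after that loss.

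Replace 12, 149 and 154 accordingly, and drop the added 25 (the addition becomes 155 − 124 = 31). If the authors did intend 154 as an evaluable minimum, they should say so, show the inputs behind it, and give 193 as the number to recruit. If the discordance rates or the independence assumption are revised, the chain and the power should be recalculated from the new inputs.

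The cost is a correction to the text. This item needs no extra enrolment and no change to the analysis.

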### Organization and statistical treatment of data

Non-parametric McNemar’s Chi-Square test will be used for paired nominal data. This test enables the comparison of the detection proportions between the two methods. Kappa coefficients will be calculated to assess the agreement between the two methods.

Differences in detecting the existence of primary interproximal caries lesions above the gingiva (sensitivity and specificity) between the iTero Element 5D system and BWX and the corresponding 90% confidence interval for the differences will be calculated. A minimum of 154 surfaces will ensure a power of 0.8, with an alpha = 0.05. Moderate agreement (Kappa≥0.5) is expected between iTero Element 5D system and radiography. Non-inferiority of the iTero Element 5D is expected as compared with radiography and evaluated by the McNemar’s Chi-Square test.

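### Every child supplies at least two surfaces, but the sample size and the McNemar test treat surfaces as independent; with positive within-child correlation, error and power are moderately off at about two surfaces per child

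*Protocol article*

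**What the plan says.** Under Inclusion criteria in the protocol article, a child must "Present at least two tooth surfaces that can be included in the study". No maximum is given.

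Under Sample calculation, the size comes from a McNemar formula for paired nominal data, adapted to non-inferiority: "Similar formulae can be obtained for the one-sided non-inferiority test by substituting" the one-sided quantile and the margin. The inputs are alpha 0.05, power 0.8, a margin of 5%, and discordant rates of 0.06% and 0.1%. The result is counted in surfaces: "So, the total number of surfaces needed for the clinical trial is 149, requiring 80 patients".

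Under Organization and statistical treatment of data, the power statement is again in surfaces: "A minimum of 154 surfaces will ensure a power of 0.8, with an alpha = 0.05". The test is McNemar's chi-square, described with the words "This test enables the comparison of the detection proportions between the two methods". It is also named as the test that will evaluate non-inferiority. Kappa and a 90% confidence interval for the differences are planned, without a stated method for the interval.

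The article mentions no intra-child correlation, design effect, cluster-adjusted test, or selection of one surface per child.

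**The concern.** The ordinary McNemar test and the sample size formula take each surface as a separate, independent pair of readings. The design guarantees that surfaces come in groups of two or more from one mouth. Within a child, the two methods share cooperation, the scan session, radiograph quality and test order. Some eligible surfaces also face each other across one contact. These features make it plausible that a disagreement between scan and radiograph on one surface goes with a disagreement in the same direction on another.

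If so, the variance of the difference is understated. The error runs towards declaring the scanner non-inferior too easily, and non-inferiority to radiography is the trial's formal inferential claim.

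**Working it through.** **Inputs from the protocol article.** p01 = 0.0006, p10 = 0.001, M = 0.05, one-sided alpha 0.05, power 0.8, 80 children, at least two surfaces each.

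**Assumption.** The within-child correlation of the paired difference (ICC) is not in the documents. It is taken as 0.1 to 0.3.

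**Step 1: reproduce the plan's size.** Let S = p01 + p10 + M = 0.0516 and D = p10 + M − p01 = 0.0504.

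n = [1.645 × √0.0516 + 0.842 × √(0.0516 − 0.0504²)]² / 0.0504² = 123.48, so 124 surfaces.

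- 124 × 1.2 = 148.8, so 149. This matches the Sample calculation total and its 25 extra surfaces.
- 123.48 / 0.8 = 154.4, which matches the 154 in the analysis section.
- The printed text "The minimum sample size required is 12 surfaces" does not reproduce. 124 is what the formula gives and what the total needs. That is a separate matter.

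The formula has no clustering term, so 124, 149 and 154 all rest on independent surfaces. Also, 149 / 80 = 1.86 surfaces per child, below the required two, which suggests that the calculation did not treat children as clusters.

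**Step 2: add clustering.** With m surfaces per child:

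- Design effect: DE = 1 + (m − 1) × ICC
- True one-sided error of a nominal 5% margin-based test: 1 − Φ(1.645 / √DE)
- Coverage of a 90% interval computed under independence: 2Φ(1.645 / √DE) − 1
- Power at effective size n: Φ[(D√n − 1.645√S) / √(S − D²)], with n = 124 / DE

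For m = 2:

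| ICC | DE | True error | 90% CI coverage | Effective size of 124 | Power |
|---|---|---|---|---|---|
| 0 | 1.0 | 5.0% | 90% | 124 | 80% |
| 0.1 | 1.1 | 5.8% | 88% | 112.7 | 77% |
| 0.2 | 1.2 | 6.7% | 87% | 103.3 | 73% |
| 0.3 | 1.3 | 7.5% | 85% | 95.4 | 70% |

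For m = 4, DE is 1.3 to 1.9 and the true error is 7.5% to 11.6%.

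**Step 3: simulation check.** The setting was 80 children, a true difference at the 5% margin and an assumed discordance of 16%. The unadjusted test with two surfaces per child rejected in 5.4% of runs at ICC 0, and in 6.5%, 7.4% and 8.0% at ICC 0.1, 0.2 and 0.3. With four per child it rejected in 7.8%, 9.9% and 12.0%. A child-level robust variance gave about 5.5% to 6.1% throughout.

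**Step 4: effective size with 80 children.**

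- m = 2: 160 surfaces, worth 160 / 1.1 = 145 down to 160 / 1.3 = 123. After 20% loss, 128 surfaces are worth 116 to 98, against 124 required.
- m = 4: 320 surfaces, worth 320 / 1.3 = 246 down to 320 / 1.9 = 168.
- m = 8: 640 surfaces, worth 640 / 1.7 = 376 down to 640 / 3.1 = 206.

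More surfaces per child therefore add information even as they inflate the error of an unadjusted test.

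**The case against.** Several objections carry weight.

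- **The excess is conditional.** It needs positive correlation of the differences between methods, not merely of caries status. Shared caries risk mostly moves both methods together on the same surface, and concordant pairs do not count in McNemar's test. The ICC is unknown, and at zero the excess vanishes. This stands, so the figures are given as a range under an assumption.
- **Examiner and randomisation add little.** The same two examiners assess everyone, so the examiner is not a child-level source of correlation. Randomisation sets only the order of two tests, and the comparison is within surface. Both stand. The argument rests on the child as the sampled unit.
- **At the planned cluster size the effect is moderate.** This stands. At ICC 0.1 the simulated excess over the zero-correlation run is about one percentage point.
- **The error figures need a margin-based test.** Ordinary McNemar tests equality, not a 5% margin. The figures describe a one-sided test against the margin, which is what the sample size formula implies. The simulation's 16% discordance is also an assumption, 100 times the 0.16% printed in the plan.
- **Interval methods are not stated.** The article gives no standard error or interval for kappa and does not say how the 90% interval is computed; an analysis plan that is not shown may settle both. Kappa's point estimate is not at issue. What remains fixed in the article is the test and the sample size.

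A reader might also infer that the effective sample shrinks as children contribute more surfaces. That would follow only if the total stayed at 149. With 80 children the total rises, and at four or eight surfaces per child the effective size exceeds 124. Nor does the article show that children with many surfaces would dominate: it sets a minimum for entry and does not say how many surfaces are analysed.

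**Conclusion.** The point holds in conditional form. The protocol fixes a test and a sample size that assume independent surfaces, in a design where every child brings two or more. That is a stated method that does not fit the design, rather than a detail left to another document.

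The direction is anti-conservative for any positive within-child correlation of the paired differences. At about two surfaces per child and an assumed ICC of 0.1 to 0.3, the consequences are those in the Step 2 table: real but moderate. The power figures also rest on the printed discordant rates and margin.

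The documents do not support the unconditional statement that the error rate exceeds 5%, since they give no ICC. They support no claim of lost effective sample at four or eight surfaces per child. Recruiting more surfaces helps power but does not restore the nominal error rate or coverage of an unadjusted analysis.

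**What to change.** 1. **Test.** Replace ordinary McNemar with a cluster-adjusted paired non-inferiority test, with the child as cluster. An Obuchowski or Durkalski type variance for the paired difference would serve, or a GEE with robust errors. Judge it against the 5% margin.
2. **Intervals.** Take the 90% interval for the difference, and any interval for kappa, from a child-level method such as a bootstrap that resamples children.
3. **Sample size.** State an assumed ICC and number of surfaces per child, apply the design effect, and restate the power. At two surfaces per child and ICC 0.1 to 0.3, 124 × 1.1 = 136.4 (137) and 124 × 1.3 = 161.2 (162) evaluable surfaces are needed. Allowing for 20% loss, 137 / 0.8 and 162 / 0.8 give 172 to 203 surfaces to recruit. If 80 children are kept, report the lower power instead.

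Changing the analysis takes a few lines of text and code and alters neither examinations nor data collection. The price is slightly wider intervals and a slightly lower stated power.

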## Introduction

Currently, dental caries is defined as a chronic and infectious disease of multifactorial etiology with a higher incidence in school-age children. According to the World Health Organization (WHO), it is considered one of the greatest pediatric health problems in the world, due to its high prevalence and significant incidence [1, 2].

For years, the main methods used in the dental clinic for diagnosing and evaluating the extent of caries lesions were: visual, tactile and radiographic clinical examination, classified as traditional or conventional detection methods [3]. For radiographic caries detection, the recommended technique is the bitewing (BWX), also called interproximal. When properly performed, it is capable of providing important information to complement the diagnosis, as interproximal radiography allows a better estimate of the more sensitive depth of proximal and occlusal caries in dentin than clinical inspection alone. Furthermore, monitoring of caries lesions can be more reliable and accurate than conventional clinical examination. However, it must be remembered that radiographic images tend to underestimate the real extent of demineralized areas [4–6].

The subjectivity of the visual clinical examination for the diagnosis of caries lesions is a great concern, so, to standardize the diagnoses, indexes can be used as a tool. ICDAS is an acronym for International Caries Detection and Assessment System, that is, an international system for the detection and assessment of caries lesions. This system seeks to standardize the detection of caries lesions and this index can be used for clinical practice, research, teaching and epidemiology [7].

Interproximal radiography helps to identify hard tissue demineralization [8], but a single radiography cannot determine whether demineralization is a sign of active or inactive caries lesions, nor is it able to distinguish between cavitated lesions and lesions with an intact surface [9].

Currently, new technologies have been developed and validated in order to complement and even surpass other methods, such as the Low-Frequency Fluorescent Laser (DIAGNOdent device—Kavo, Germany), the measurement of electrical resistance offered by the dental element (ECM device—LODE, Netherlands), the DIFOTI device, Quantitative Light-Induced Fluorescence (QLF) and Computed Tomography [10, 11].

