### Clinical protocol

The attendance of volunteers will follow the following phases:
Anamnesis and Clinical Examination;Verification of eligibility criteria (inclusion and exclusion criteria);Talk with those responsible to inform if the volunteer fits or not the research inclusion criteria. If the volunteer does not fit, he/she/they will be referred to the discipline of Pediatric Dentistry at *Universidade Metropolitana de Santos*;Signature of the Informed Consent Form by the guardians of patients who meet the inclusion criteria. Application form;Visual Inspection (ICDAS);Intraoral Scan: volunteers will be scanned intraorally (iTero Element 5D System). The order of iTero 5D and BWX assessment will be performed according to the study Groups (1 or 2);Radiographic Evaluation: BWX Radiographs;Caries Assessment Form.

The study ends when the volunteers complete all phases of the protocol and follow-up, if necessary. Clinical evaluation and subsequent treatment, if indicated, will be performed upon completion of the study.

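### Sensitivity and specificity differences between iTero and bitewing radiography are planned with no reference standard and no reference-free method, so no planned analysis identifies them

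*Protocol article*

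**What the plan says.** The section Organization and statistical treatment of data in the protocol article commits to "Differences in detecting the existence of primary interproximal caries lesions above the gingiva (sensitivity and specificity) between the iTero Element 5D system and BWX", with a 90% confidence interval for each difference. The same section plans McNemar's test on the detection proportions of two methods and kappa for their agreement. It expects a kappa of at least 0.5 and non-inferiority of iTero to radiography, judged by McNemar's test. It also states: "A minimum of 154 surfaces will ensure a power of 0.8, with an alpha = 0.05".

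The Abstract and Introduction present ICDAS, iTero and BWX as three methods to be compared, and the aim is to find the best diagnostic strategy among them. The section Clinical protocol lists the phases: history and clinical examination, eligibility, consent, ICDAS, scan, radiograph and form. It ends with "The order of iTero 5D and BWX assessment will be performed according to the study Groups (1 or 2);Radiographic Evaluation: BWX Radiographs;Caries Assessment Form". Clinical evaluation and any treatment follow once the study is complete.

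On radiographs, the Introduction warns that "it must be remembered that radiographic images tend to underestimate the real extent of demineralized areas", and that a single radiograph cannot separate cavitated lesions from lesions with an intact surface.

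The Sample calculation uses a paired McNemar formula in its one-sided non-inferiority form, with inputs described as an "assumed detection rate". It gives no prevalence, sensitivity or specificity.

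**The concern.** Sensitivity is the proportion positive among truly carious surfaces, and specificity the proportion negative among truly sound ones. Each therefore needs a disease status that does not come from the two tests being compared. The document names no such status, and it names no method that does without one.

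The analyst would then have to choose a truth after the fact, and the choice decides the answer. The obvious candidate is BWX, the non-inferiority comparator. Using it would report disagreement with BWX as diagnostic error by iTero. The detection comparison leans the other way: over-calling by iTero counts in its favour. Neither supports a statement that one method is more accurate, or that it is the best strategy.

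**Working it through.** **1. The plan's own figure.** Inputs from Sample calculation: p01 = 0.06% = 0.0006, p10 = 0.1% = 0.001, margin ("non-inferiority margin M = 5" per cent) M = 0.05, one-sided alpha 0.05 (z = 1.645), power 0.8 (z = 0.842).

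- p01 + p10 + M = 0.0516, and p10 + M − p01 = 0.0504.
- n = [1.645·√0.0516 + 0.842·√(0.0516 − 0.0504²)]² / 0.0504² = 123.5, rounded up to 124 surfaces.
- Allowing for 20% dropout by division: 123.48 / 0.8 = 154.4, which is the 154 of the analysis section.
- Allowing for it by multiplication: 124 × 1.2 = 148.8, which is the 149 of Sample calculation. That mismatch is a separate matter.

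So 154 is the dropout-inflated size for the paired detection comparison over all surfaces. No quantity conditional on disease status enters it.

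**2. What could supply the truth.**

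- *BWX:* a method under comparison, and one side of the planned difference.
- *iTero:* likewise.
- *ICDAS:* a method under comparison. The Introduction itself says that BWX estimates lesion depth better than clinical inspection alone.
- *History and clinical examination:* listed before eligibility, with no reference role stated.
- *Later clinical evaluation or treatment:* after the study, with no verification role stated.

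**3. BWX as truth, in general.** Let a = proportion of surfaces positive on both, b = iTero only, c = BWX only, d = negative on both.

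- BWX: sensitivity and specificity are both 100% by definition.
- iTero: sensitivity = a/(a + c), so the difference from BWX is −c/(a + c).
- iTero: specificity = d/(b + d), so the difference is −b/(b + d).
- Detection difference, iTero minus BWX: b − c.

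Neither accuracy difference can exceed zero, whatever iTero does. The detection difference can take either sign.

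**4. Illustration (assumed cells).** a = 24%, b = 10%, c = 6%, d = 60%.

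- Detection: iTero 24 + 10 = 34%, BWX 24 + 6 = 30%, difference +4 points.
- iTero sensitivity against BWX: 24/30 = 80%, difference −20 points.
- iTero specificity against BWX: 60/70 = 86%, difference −14 points.
- Kappa: observed agreement 0.84; expected 0.34 × 0.30 + 0.66 × 0.70 = 0.564; kappa = (0.84 − 0.564)/(1 − 0.564) = 0.63, within the plan's expectation of at least 0.5.

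**5. How the size depends on the assumption.** Take the printed discordances literally, with p10 as iTero only and p01 as BWX only, and again assume 30% BWX-positive. iTero sensitivity is then 1 − 0.0006/0.30 = 99.8% and specificity 1 − 0.001/0.70 = 99.9%. The size shrinks to almost nothing, but the direction stays fixed. The distortion therefore runs from negligible to tens of points, depending on a disagreement rate that only the data will show.

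**The case against.** **Sensitivity and specificity can be estimated without a gold standard.** A latent-class model for three tests can do so, under assumptions about dependence between tests. This stands: a reader might infer that the quantities can never be estimated, and that goes too far. The supportable statement is that the document specifies neither a reference nor such a method.

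**BWX is not the only possible reference.** Against ICDAS, BWX would not be perfect by construction. True, but the plan does not name ICDAS as reference and lists it as a competitor. The 80% and 86% describe one assumed scenario.

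**The article is condensed.** Case definitions and the content of the form may sit in a fuller protocol, and detail of method in an analysis plan. That excuses missing detail. It does not supply a truth measurement that the phase list does not collect.

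**Power.** A reader might infer that the plan claims 0.8 power for sensitivity and falls short because only carious surfaces count. The documents do not support this. The sentence on 154 surfaces names no endpoint, and the figure reproduces for the detection comparison. No prevalence is given, so the number of carious surfaces is unknown. The plan's formula is also unreliable at these rates: even with 77 carious surfaces (half of 154), only 77 × 0.0016 = 0.12 discordant surfaces are expected. An exact calculation with a one-sided score test and the same inputs gives power of about 0.00, 0.04, 0.96 and 0.96 at 31, 46, 62 and 77 surfaces. No shortfall can be stated. What remains is that the sentence directly follows the one on sensitivity and specificity and should name its endpoint.

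**The Introduction on radiographs.** It speaks of underestimated extent. A reader might take this as an admission that BWX misses lesions, but the text does not say so. It is a reason for caution about BWX as truth, no more.

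**Most of the analysis is sound without a truth.** McNemar's test, the non-inferiority comparison and kappa can all be carried out. This stands, and it is why the correction is small.

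**Conclusion.** The point holds in this form: the plan names differences in sensitivity and specificity as results, while no listed procedure gives a disease status independent of the three methods and no reference-free method is named. No planned analysis identifies these differences. This rests on the text alone and needs no numerical assumption.

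The consequence of falling back on BWX is certain in direction, since iTero could only tie or lose, and uncertain in size. With the assumed 24/10/6/60% cells it is −20 and −14 points while detection favours iTero by 4 points; with the printed discordances it is close to zero.

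The point does not invalidate the trial or its paired detection and agreement analyses, and it carries no claim about power for sensitivity or specificity. It limits what may be concluded: detection and agreement, not accuracy and not which strategy is best.

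**What to change.** In Organization and statistical treatment of data:

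- Replace the sensitivity and specificity differences with the paired difference in detection proportion, iTero minus BWX, and its 90% confidence interval. This is the measure that the planned McNemar non-inferiority comparison already addresses.
- Add positive and negative percent agreement of iTero with BWX, each with a confidence interval and labelled as agreement.
- Report iTero-only and BWX-only surface counts separately. The detection comparison rewards over-calling by iTero, and these counts make that visible, though only descriptively.
- State that the 0.8 power refers to the detection-proportion comparison only.

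In the Abstract and Introduction, word the aim as a comparison of detection and agreement in place of a search for the best strategy, and hold the conclusions to the same limit. A latent-class model on the three methods may be added as an exploratory analysis with its assumptions stated; it is optional.

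Cost: wording only, with no new procedure or visit. The downside is a weaker claim than diagnostic accuracy.

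### Non-inferiority of iTero to bitewing radiography is assigned to McNemar's chi-square, an equality test that does not contain the 5% margin used for the sample size

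*Protocol article*

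**What the plan says.** The section on the sample calculation of the protocol article starts from the McNemar sample size equation and adapts it: "Similar formulae can be obtained for the one-sided non-inferiority test by substituting" a one-sided normal quantile and a discordant rate increased by M. The settings are "where significance level *α* = 0.05" and "non-inferiority margin M = 5%, assumed detection rate"; power is 0.8. The discordant rates are given as "assumed detection rate *p*_01_ = 0.06%, *p*_10_ = 0.1"%.

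The section on the organization and statistical treatment of data then introduces McNemar's chi-square for the paired nominal data: "This test enables the comparison of the detection proportions between the two methods". For the iTero and radiography differences in sensitivity and specificity, "the corresponding 90% confidence interval for the differences will be calculated". It closes with the expectation of non-inferiority: "Non-inferiority of the iTero Element 5D is expected as compared with radiography and evaluated by the McNemar’s Chi-Square test". This section mentions neither the 5% margin, nor a shifted null hypothesis, nor a decision rule.

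**The concern.** The quantity that was sized and the test that is named do not match. The sample calculation puts the null hypothesis at a 5-point deficit for iTero. The test named in the analysis puts it at no difference. A significant McNemar result shows that the methods differ; a non-significant one says nothing about whether a deficit of 5 points has been ruled out.

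The article's only non-inferiority claim depends on this step. With no rule stated, the natural misreading is that a non-significant result means non-inferior. Such a reading rewards weak data: the fewer the discordant pairs or surfaces, the easier it is to pass.

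**Working it through.** **1. The article's own figure.** Inputs from the sample calculation: p01 = 0.0006, p10 = 0.001, M = 0.05, one-sided alpha 0.05 (z = 1.645), power 0.8 (z = 0.842). I take p10 as found by iTero only and p01 as found by radiography only.

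- p01 + p10 + M = 0.0516
- p10 + M - p01 = 0.0504
- n = [1.645 × √0.0516 + 0.842 × √(0.0516 - 0.0504²)]² / 0.0504² = 123.5, so 124
- 124 × 1.2 = 148.8, so 149, the stated total (124 + 25)

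The total is thus reproduced, and only by a formula that contains the margin.

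**2. The named test.** With b surfaces positive by radiography only and c by iTero only, McNemar's statistic is (b - c)²/(b + c). Its null is p01 = p10. M does not appear in it.

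**3. The printed rates do not help.** They imply 0.0016 × 149 = 0.24 expected discordant pairs. McNemar's test is then non-significant with probability of about 1.00 and carries no information about the margin. Other discordance levels therefore have to be assumed.

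**4. What the misreading would cost.** Assume 149 independent surfaces and iTero truly 5 points worse, so p01 - p10 = 0.05. The table gives the probability that the two-sided 5% McNemar test (no continuity correction) is non-significant. A valid non-inferiority rule should pass about 5% of the time here.

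| Assumed discordance p01 + p10 | McNemar non-significant |
|---|---|
| 5.2% | 10% |
| 8% | 41% |
| 10% | 51% |
| 16% | 66% |
| 21% | 73% |
| 25% | 77% |

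With continuity correction the figure is 27% at 5.2% discordance and 80% at 21%. The 21% row corresponds to kappa 0.5 if each method is positive on 30% of surfaces (assumed): chance agreement 0.09 + 0.49 = 0.58, observed agreement 0.58 + 0.5 × 0.42 = 0.79, discordance 0.21.

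**5. A rule that uses the margin.** In the same setting, requiring the lower limit of a Wald 90% interval to exceed -5 points passes 5% to 6% of the time at 16% to 25% discordance, but about 8% at 8% and about 12% at 5.2%. A paired score test with its null at -5 points passes 4.8% of the time at 16% and 5.2% at 5.2%.

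**6. One data set, two answers.** Take n = 149, b = 12, c = 5. McNemar's chi-square is 7²/17 = 2.88, below 3.84, so not significant. The difference is -7/149 = -4.7 points. Its standard error is √(17/149 - 0.047²)/√149 = 0.0274, so the 90% interval is -9.2 to -0.2 points. No difference is shown, and neither is non-inferiority at 5%.

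**The case against.** The best defence is that the test's name is shorthand. The sample calculation calls its equation a McNemar equation and then shifts it by M, so the authors may mean a margin-shifted, one-sided test. They also plan a 90% interval, the right width for a one-sided 5% decision. The article is condensed, and the exact statistic could stand in an analysis plan that is not shown.

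Part of this stands. It would be wrong to say that the plan as a whole ignores the margin: the margin is in the sizing and is not carried into the analysis text. A reader might also infer that the article intends to take a non-significant result as non-inferiority. It nowhere says so; it gives no rule at all. The error rates above therefore describe a possible misreading, not a stated procedure.

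The defence does not remove the problem. The analysis section names the ordinary chi-square, describes it as comparing two proportions, and assigns the non-inferiority conclusion to it. The interval is attached to other quantities and to no threshold. This is a stated choice of test, not detail left to a later plan, and an analysis plan that followed the sentence would inherit it.

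**Conclusion.** The point holds: as written, the named test cannot establish non-inferiority, and the analysis text does not match the margin-based sizing.

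If non-significance were read as non-inferiority, the false-positive rate at the margin would be about 10% to 77% instead of 5%. This rests on 149 surfaces treated as independent, a two-sided 5% test, and discordance between 5.2% and 25%. The documents give no usable discordance figure, so the whole range should be quoted. Quoting only its upper part, 66% to 77%, would lean on an assumed share of positive surfaces and leave out low discordance. That the test lacks the margin depends on none of these assumptions.

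**What to change.** Replace the closing sentence of the analysis section with a rule of this kind: non-inferiority is concluded if the lower limit of the two-sided 90% confidence interval for the paired difference in detection proportion (iTero minus radiography) lies above -5 percentage points. A one-sided 5% paired score test with its null at -5 points is the equivalent. A score-type interval is preferable to Wald because of the error of about 12% at low discordance. Keep McNemar's test for difference only, and state that its non-significance is not evidence of non-inferiority.

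The change costs a few lines of text and needs no new type of data, but the rule is harder to pass. Under the printed rates the sizing already fits it (124 surfaces before drop-off). If discordance were 16% to 21% and the methods were truly equal, power with 149 independent surfaces would be only about 46% to 38% by the Wald limit. At 21%, 80% power would need about (1.645 + 0.842)² × 0.21/0.05² ≈ 520 surfaces. The authors should disclose this and say what discordance they expect. Clustering of surfaces within a child is a separate matter and is not counted here.
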